### Postoperative care

- Analgesia will be provided (see 4.2)

- Men will not be discharged if they experience severe pain, cannot walk independently or have evidence of bleeding through the dressing

- Men will be instructed not to share their pain medications. The postoperative visit will be used to monitor analgesia use.

- Men will rest for a minimum of 30 minutes or longer until they feel able to return home . All men will be examined by a physician or health worker prior to discharge and a Form 04 completed.

- Men will be provided with instructions on wound care and analgesia, and this will be reviewed with them before discharge (Postoperative patient Information Sheet 46).

.

- At time of discharge, men will be offered free transport. Men who decline or do not require transport (residence close to the Rakai Health sciences program clinic) will be advised to be accompanied by a family member, friend or Rakai Health sciences program staff.

- Free postoperative overnight stay facilities will be made available, if men choose to avail themselves of this service.

### Asepsis

- All theater staff will be trained in aseptic procedures, including documentation.

- Steam Indicators, Biological Indicators, autoclave tracking labels and instrument lists will be used to insure sterility, tracing of instruments and QC.

### Emergency procedures:

- A crash cart, IV and oxygen will be available for emergencies.

- The main potential emergency is excessive bleeding, which will be controlled by ligation of vessels and by pressure. If uncontrolled bleeding persists, a pressure dressing will be applied, and a catheter inserted if needed. If these measures do not control bleeding, an IV will be inserted and oxygen provided if needed, and the patient will be transported to hospital (Kalisizo Hospital < 5 minutes away; larger hospitals in Masaka (Masaka Hospital or Kitovu, a mission hospital ~30 minutes) away, if needed.

- Anaphylactic reaction to the local anaesthetic will be managed with epinephrine, oxygen, IV and transport to the Hospital, if needed.

## Concomitant Medications

### Analgesia

- Experience has shown that postoperative Tramadol is not needed for pain control due to the long action of the local anaesthesia. Also, Tramadol can delay discharge due to drowsiness Therefore postoperative and subsequent analgesia will use Acetominophen 325 to 650 mg, every 4-6 hours, as needed.

Postoperative analgesia with Tramadol hydrochloride 50-100 mg stat will be provided if Acetominophen does not control postoperative pain.

Men will be evaluated by a home visit the next day, and if moderate to severe pain is reported, Tramadol hydrochloride 50 - 100mg- will be dispensed.

### Treatment of Infections

*1. Treatment of STDs and Balanitis*.

- we will use symptom-based management of symptomatic infections at time of survey. In addition, syphilis treatment will be provided on the basis of serology.

- The regimen of treatment will, where possible, use directly observed, single oral therapies developed and evaluated in the STD Control Trial. The treatment algorithms include the following:

1) *GUD*. Therapy will cover *T. pallidum, H. ducreyi* and HSV-2: azithromycin 1 gram, ciprofloxacine 500 mg, IM benzathine benzylpenicillin 2.4 million units if there is serologic evidence of syphilis, acycolvir 400mg t.d.s for five days for active herpes (per PDR 2003), other therapy may be provided as medically indicated.

2) Urethral discharge/dysuria in men. Therapy will cover *N. gonorrohoeae*, and *C. trachomatis*: azithromycin 1 gram, ciprofloxacine 500 mg.

3) *Balanitis* treatment will consist of metrondizaole 2 grams stat for anaerobes, and topical clotrimazole for *C. albicans*.

*2. Pre- or post-operative penile infections* (other than balanitis) will be treated with azithromycin and ciprofloxacin. Indications for treatment are: a) clinical evidence of infection among men presenting for circumcision or after circumcision, and b) symptoms suggestive of current STDs (GUD, discharge, dysuria), reported by men during surveys or at post-circumcision visits, in both arms. Uganda MoH standard of care will be used for partner notification (MoH-STD Form 4)- Form 35 and provision of free treatment.

### Treatment of Anemia

Men with hemoglobin < 8 grams/dL, will receive iron/folate supplements and presumptive treatment for malaria and helminths using standard MoH regimens for treatment of anemia in adults. Enrollment and randomization will be deferred until the hemoglobin is increased to  8 grams/dL. If the patient does not respond to therapy, they will be referred for investigation of persistent anemia. Anemia resulting from hemoglobinopathies such as sickle cell disease will be referred.

# CLINICAL AND LABORATORY EVALUATIONS

## Screening Evaluations

### Screening Interview and Exam

- Consent for screening was obtained (Form I)

- An interview ascertained symptoms of penile pathology and other relevant medical conditions. (Form 01)

- All participants were asked to provide blood for HIV testing and hemoglobin determination to assess eligibility prior to enrollment. Blood was stored for future STD testing with other funds (See Lab methods).

- An exam was performed to verify circumcision status, and to diagnose infection, balanitis, phimosis and anatomical abnormalities (Form 01).

- Swabs were collected for future assays such as PCR, HPV and M-PCR for GUD (under separate funds).

### Eligibility

-Eligibility Screening consisted of willingness to participate, consent to circumcision and to randomization of timing of circumcision, confirmation of uncircumcised status, confirmation of HIV status, and confirmation of Hgb 8.0 g/dL. Thus, eligibility could only be determined after interview, exam and HIV/Hgb test which were recorded in the Eligibility Verification Form 22.

### Enrollment and Randomization

- After confirmation of eligibility men were consented for enrollment (Form I. b.), randomized and given a Post-Randomization Information Sheet (Form II) to inform them of their study arm allocation. Random allocation was recorded on Form 18.

### Sociodemographic and Behavioral Interview

- Cohort participants routinely complete a sociodemographic, behavioral and health follow up interview during annual cohort visits (Form 48.). For cohort participants who completed this interview within six months of enrollment, no re-interview was needed. Cohort participants interviewed more than 6 months prior to enrollment were re-interviewed to up date behavioral information.

- Non-cohort participants were interviewed using the RCCS baseline interview Form 02a

## Evaluation Related to Surgery

### Preoperative Assessment

- Prior to circumcision, men are asked to consent to surgery (amended Form III), assessed by a clinical health worker or a physician. The clinical health worker takes a general medical history, conducts a general systems exam and a genital exam (Form 03). The assessment includes general medical history and general systems exam and a genital exam (Form 03). The clinical health worker or physician examines the penis and ensures that the patient is fit for surgery. Any infection or other abnormality which might be a contraindication for surgery is treated per protocol or by referral, and surgery is rescheduled.

- Swabs are taken for future assays such as PCR, HPV and culture

### Surgery

- The foreskin with the frenulum facing upwards, will be placed on a board. The width and length will be measured in centimeters and recorded.

- Two separate quadrants with full thickness sections of the foreskin will be placed in safe-fix or other appropriate fixative and labeled with the ID#.

- A Surgical Record form (Form 06), will record the surgery and post-operative status prior to discharge.

## Post-Surgical Evaluations for Intervention Arm, and Post-Enrollment Evaluations for Control Arm Participants in stage 2

### Post-operative Evaluations

The schedule of postoperative evaluations for stage 2 of the trial is given in Figures 2

1st post operative visit <48 hrs of surgery.

2nd post operative visit at 7 ± 2 days following surgery.

3rd post operative visit 3-6 weeks following surgery

Unscheduled visits can occur at any time if a participant experiences problems. Participants can contact the project via community counselors who are equipped with cell phones. If wound healing is incomplete at visit 3, men will be followed weekly until wound healing is certified.

These visits, which can take place in the participant’s home or at a convenient central location (“hub”), will record AEs, symptoms, resumption of intercourse, assessment of condom use, examination of the wound and collection of a culture swab if there is evidence of infection, evaluation of wound healing and certification if healing is complete.

Under this amendment, all HIV+ subjects and a sub sample of about 200 HIV negative men enrolled in the Gates funded trial will be followed at weekly intervals until complete wound healing is documented. At each visit, including the currently scheduled one and four week visits, the wound will be inspected using a magnifying glass, and records maintained of the development of scar tissue, scabs, breaches in skin integrity, adsorption of sutures, stitch sinuses, wound dehiscence, infection, hematoma and bleeding. The anatomic site of any problems will be noted. Follow up will continue until all AEs have been resolved. Records will also be maintained of wound care, resumption of intercourse and condom use. A SOP will be developed to ensure uniform certification of wound healing by clinical officers. Digital photographs may be taken to document lesions with the participant’s permission and will not include identifying facial features.. The participant will be asked to sign the photograph indicating their permission.

Consideration will be given to use of Imalux Optical Coherence Tomography (OCT) to monitor scar formation and depth (1-2 mm). However, the cost of this equipment is $60,000 and there would be delays in purchase, shipping and training for use. Therefore, rather than delay circumcision in HIV+ men, we propose to monitor healing visually until decisions on purchase of OCT equipment have been made.

At each weekly postoperative visit 5 mL of venous blood will be collected for determination of HIV viral load to assess whether surgery affects men’s viremia.

Scheduled follow up - Both arms

All men were seen 4-8 weeks post-Enrollment. For intervention arm, this coincided with post operative visit 3 to certify healing.

All participants are followed up at 6, 12 and 24 months to ascertain study end points, including HIV status (Form 12). HIV+ men and their female partners will be followed at 18 months to ascertain study end points at a time earlier than 2 years. For masking purposes, a subsample of HIV-negative men enrolled in the Gates sponsored trial, and their female partners, will also have an additional follow up at 18 months.

Evaluations at the time of premature discontinuation

If participants withdraw from the study, this will be recorded on a withdrawal form (Form 14).

## Laboratory Methods for Evaluations/

The samples are tested by two separate EIAs, and if both EIAs are negative or both are positive, the participant can be enrolled into the respective tirals. . If the EIAs are discordant, HIV status will be determined by western blot, prior to enrolment into the appropriate trial. Indeterminant Western blots will be tested by PCR.

**HIV Status.**

All participants who were tested using Rapid HIV test had their HIV results confirmed using two separate EIAs with Western blot confirmation of discordant EIA tests*.* New seroconverters are also confirmed by Western blot. Tests are run in batches and technicians blinded. If a participant refuses to provide blood during follow up, we request a urine sample for HIV testing using a urinary EIA and Western blot.

**STD Testing.** Serology is performed for syphilis and RPR-positive samples are confirmed by treponemal-specific tests such as TPHA, TPPA, or FTA-ABS.

Using other funding and separate protocols, stored samples will be tested in future for infections such as herpes simplex virus type-2 (HSV-2) infection using test kits such as the Focus EIA. *Neisseria gonorroheae* and *Chlamydia trachomatis* will be detected by PCR or equivalent methods on male urine samples Since GUD is a cofactor for HIV acquisition, all ulcers will be swabbed for future testing by PCR or equivalent methods for syphilis, *H. ducreyi* and HSV-2 in U.S.A.

**Hemoglobin**

Hemoglobin is determined using portable hemoglobinometers. A finger stick fresh blood sample is collected in a cuvette and read within 10 minutes. .

## Behavioral Research Methods for Evaluations.

Behavioral studies have already been conducted on circumcision acceptability and perceptions of risk and benefit with other funds. Behavioral research has been conducted concurrently with the trial to assess participant and community beliefs and attitudes towards circumcision, to evaluate the experience of men receiving surgery and the attitudes of control subjects allocated to delayed circumcision. These studies also provide qualitative information on participant and community beliefs about possible protective effects of circumcision which might affect behaviors, including disinhibition. Separate informed consents were developed for these behavioral study participants. Subjects included male trial participants and non-trial participants, and females (irrespective of whether their partners are trial participants or not). The methods include:

*Structured Interviews* are conducted with male trial participants at enrollment and in follow up surveys to ascertain risk behaviors (number and types of partners, coital frequency, condom use, alcohol use etc.), self-perceived HIV risk and use of VCT.

*Rapid Ethnographic Assessment (REA).* For exploration of norms, values and meanings regarding circumcision, we conducted in-depth interviews and focus group discussions with men and women aged 15-49 . This information will assist in the development of education messages on the benefits and risks of circumcision, and will facilitate interpretation of information obtained by the structured interviews. Application of multiple data collection methods permits “triangulation”, and validation of findings. The domains to be specifically explored include perceptions, facilitators and barriers to circumcision, the relationship of circumcision to sexuality, religion, and risk for HIV/STDs. Behavioral data will be collected throughout the study to adjust our education and community motivation programs as needed.

*In-depth interviews* are conducted with male and female key informants from different age groups (15-19, 20-29, 30-39, 40-49) to provide insights into the experiences, attitudes, perceptions and opinions of individuals. A total of approximately 40 informants (~5 male and ~5 female from each of the age groups), were identified through purposive sampling, based on informant’s enculturation and involvement in their respective communities. The sample included representation by residence, ethnicity, religion, economic activities, and education. Open-ended questions are used to encourage conversation and enable probing, to elicit information on experiences and on disinhibition. Although females are not enrolled in the trial, we believe it is crucial to enroll them in the REA, since their attitudes and support will be critical for male circumcision acceptance.

*Focus group discussions*. We conducted approximately 32 focus groups each stratified by marital status and gender in age groups 15-19, 20-29, 30-39 and 40-49 to elicit information on shared beliefs, opinions, group concerns and expectations, group knowledge and awareness, and other normative perspectives. The primary objective is to elicit normative perceptions of circumcision, terminology used locally in discussing circumcision, and opinions regarding its acceptability as an HIV/STD preventive measure. Focus group discussions with community gatekeepers, stakeholders as well as community members were held.

*Qualitative data management and analyses* : The ethnographic data is transcribed and translated by experienced Rakai Health sciences program personnel. The word processed text is then coded and organized using NVIVO. Further editing is done in Uganda and the US. Data analysis/summaries will be completed in the US and will focus on barriers to circumcision, means for overcoming barriers, incentives that might be acceptable, and perceptions or beliefs which might lead to behavioral disinhibition.

# DATA COLLECTION, SITE MONITORING AND ADVERSE EXPERIENCE REPORTING

## Records to Be Kept.

Records for the Gates Trial are kept in secure filling cabinets, separate from the records of the NIH trial participants. The records to be kept for each subject are consent and information forms (I-V) and record forms 01-16. These are summarized in Tables 2.a. and 2.b. Files are maintained on each participant to provide a chronological record of all forms used. Files are organized by study number and maintained in locked cabinets in secure storage rooms.

## Data Management

- Data management is conducted by the Rakai Health Sciences Program and JHU. We have extensive experience managing large data sets. We are using existing Rakai Health Sciences Program census and survey forms, with supplementary record forms specific to the trial. Forms are translated into Luganda and printed in Uganda.

- All participants have a household census enumeration. Census files are used to generate updated data to provide computer generated tracking forms, and pre-printed labels for all questionnaires and samples.

- Data collection is conducted by highly trained and experienced full-time, same-sex interviewers. Field editors check all completed questionnaires and query inconsistencies or errors in the field so that interviewers can return to re-interview subjects and correct errors immediately.

- Subjects are identified by photo IDs and have permanent, unique alphanumeric check digit study ID numbers which prevent keying errors. Subjects enrolled from the cohort also have location numbers for community, household and census resident numbers to facilitate tracing.

- Data entry is done in Rakai Offices using Foxpro screens with programmed range and consistency checks. All lab data and questionnaires are double entered.. The data entry system is adapted for this trial by experienced data managers in Entebbe and JHU, and relational data bases will be constructed.

- The data is sent by FTP or zip files to JHU. Further data editing and cleaning are conducted at JHU and queries sent to Uganda for clarification and error correction.

- Security is maintained by storing all data files on codeword protected machines accessible only to senior data managers and analysts.

- A central manual of operations and standard operating procedures were written and updated as need arose.

- Adherence to protocol is assessed by periodic checks on consent forms and hard copy study instruments, as well as data sets.

## Clinical Site Monitoring and Record Availability

Monitoring will be conducted at intervals to be determined by the Gates Foundation and the DSMB.

All study hard copy records will be available to site monitors and will be maintained in individual chronological files on all study participants. Computer files may be accessed on site during a monitoring visit.

## Serious Adverse Event Reporting

The occurrence of severe adverse events (SAEs) is recorded at every post-randomization visit.

### General Definitions

An AE is defined as “any untoward medical occurrence in a participant and that does not necessarily have a causal relationship with the treatment. An AE can be any unfavorable and unintended sign (including an abnormal laboratory finding), symptom or disease temporarily associated with the beginning of the treatment (i.e., following randomization).**”** In this trial we recorded AES during or after screening.**”** Adverse events during screening and prior to randomization that result from study participation were also reported.

- The adverse events are defined in Table 3 and AE notification is given in form 11a.

### Severity of AEs

- The severity of AEs is characterized as:

. *mild* (transient and not affecting activity),

*. moderate* (requiring modification of activity or additional medical /minor surgical/intervention),

*. severe* (resulting in: death, life threatening condition, incapacitating symptoms which require bed rest, hospitalization, significant medical/surgical interventions or which result in persistent significant disability/incapacity).

- All severe occurrences are considered serious adverse events (SAEs) for reporting purposes, consistent with FDA definitions as follows:

. Life threatening: substantial risk of dying at the time of the AE

. Hospitalization (initial or prolonged): if admission to hospital or prolongation of hospital stay results from the AE.

. Disability: if the AE resulted in a significant, persistent or permanent change, impairment, damage or disruption in the patient’s body function/structure, physical activities or quality of life.

. Intervention required to prevent permanent impairment or damage: if it is suspected that the treatment may result in a condition which required medical or surgical intervention to preclude permanent impairment or damage to the patient.

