**Table 3. Study Definition of Adverse Events**

| Adverse Event Type | Description of Adverse Event Type | Severity  and Codes |
| --- | --- | --- |

|  |  |  |
| --- | --- | --- |

| A. During Surgery |  |  |
| --- | --- | --- |

| Pain | Minor, not requiring additional anaesthesia | Mild (APS1) |
| --- | --- | --- |

|  | Moderate/severe controlled with additional anaesthesia* | Moderate (APS2) |
| --- | --- | --- |

|  | Severe, not controlled by additional anaesthesia | Severe (APS3) |
| --- | --- | --- |

| Excessive bleeding | More bleeding than usual, but easily controlled | Mild (ABL1) |
| --- | --- | --- |

|  | Bleeding that requires pressure dressing to control | Moderate (ABL2) |
| --- | --- | --- |

|  | Blood transfusion or transfer to another facility for management required | Severe (ABL3) |
| --- | --- | --- |

| Anesthetic-related event | Palpitations, vaso-vagal reaction or emesis | Mild (AAN1) |
| --- | --- | --- |

|  | Reaction to anesthetic requiring medical treatment in study clinic but not transfer to another facility | Moderate (AAN2) |
| --- | --- | --- |

|  | Anaphylaxis or any reaction requiring transfer to another facility | Severe (AAN3) |
| --- | --- | --- |

| Excessive skin removed | Adds time or material needs to the procedure, but does not result in any discernable adverse condition | Mild (AES1) |
| --- | --- | --- |
|  | Skin is tight, but additional operative work not necessary | Moderate (AES2) |

|  | Requires re-operation or transfer to another facility to correct the problem | Severe (AES3) |
| --- | --- | --- |

| Damage to the penis | Mild bruising or abrasion, not requiring treatment | Mild (ADP1) |
| --- | --- | --- |

|  | Bruise or abrasion to the glans or shaft of the penis requiring pressure dressing or additional surgery to control | Moderate (ADP2) |
| --- | --- | --- |

|  | Portion or all of the glans or shaft of the penis severed or burned by electrocautery | Severe (ADP3) |
| --- | --- | --- |

| B. First Month Post-Surgery |  |  |
| --- | --- | --- |

| Pain | Symptoms of pain requiring bed rest for less than half the day | Mild (BPA1) |
| --- | --- | --- |

|  | Pain requiring bed rest for more than half day | Moderate (BPA2) |
| --- | --- | --- |

|  | Excruciating pain requiring total bed rest | Severe |
| --- | --- | --- |

| Excessive bleeding | Dressing or other materials (for example underwear) spotted but dry | Mild (BBA1) |
| --- | --- | --- |

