|  | Dressing or other materials wet with clotted blood requiring change of dressing | Moderate (BBA2) |
| --- | --- | --- |

|  | Dressing or other materials soaked with blood with obvious active bleeding requiring surgical exploration or transfusion | Severe (BBA3) |
| --- | --- | --- |

| Excessive skin removed | Client concerned but no discomfort on erection | Mild (BES1) |
| --- | --- | --- |

|  | Causes slight disconfort on erection but surgical correction not necessary. | Moderate (BES2) |
| --- | --- | --- |

|  | Interferes with life and surgical correction necessary | Severe (BES3) |
| --- | --- | --- |

| Insufficient skin removed | Prepuce partially covers the glans only when extended | Mild (BIS1) |
| --- | --- | --- |

|  | Prepuce still partially covers the glans and re-operation is required to correct | Moderate (BIS2) |
| --- | --- | --- |

|  | Not applicable |  |
| --- | --- | --- |

|  |  |  |
| --- | --- | --- |

| Swelling/Hematoma | More swelling than usual, but no treatment needed | Mild (BSH1) |
| --- | --- | --- |

|  | swelling requiring surgical exploration but no evidence of active bleeding | Moderate (BSH2) |
| --- | --- | --- |

|  | Rapidly expanding Heamatoma suggesting active bleeding requiring surgical exploration or referral | Severe (BSH3) |
| --- | --- | --- |

| Damage to the penis | Mild bruising or abrasion, not requiring treatment | Mild (BDP1) |
| --- | --- | --- |

|  | Bruise or abrasion to the glans or shaft of the penis requiring pressure dressing or additional surgery to control | Moderate (BDP2) |
| --- | --- | --- |

|  | Portion or all of the glans or shaft of the penis severed | Severe (BDP3) |
| --- | --- | --- |

| Infection | Pain and erythema with no obvious swelling | Mild (BIN1) |
| --- | --- | --- |

|  | Painful swelling with erythema or elevated temperature or purulent wound discharge | Moderate (BIN2) |
| --- | --- | --- |

|  | Cellulitis or wound necrosis | Severe (BIN3) |
| --- | --- | --- |

| Delayed wound healing | Healing takes longer than usual, but no extra treatment necessary | Mild (BDW1) |
| --- | --- | --- |

|  | Additional non-operative treatment required | Moderate (BDW2) |
| --- | --- | --- |

|  | Requires re-operation to correct | Severe (BDW3) |
| --- | --- | --- |

| Appearance | Client concerned, but no discernable deformity | Mild (BAP1) |
| --- | --- | --- |

|  | Minimal deformity does not require re-operation | Moderate (BAP2) |
| --- | --- | --- |

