### Reporting of AEs

- All AEs are ascertained and documented by Program medical officers

- All deaths and SAEs are notified to the Ugandan and U.S. PIs within 48 hours, by e-mail or fax.

- The U.S. and Ugandan PIs then notifies the relevant IRBs (Johns Hopkins, Columbia University and Uganda Virus research Institute) in writing as soon as possible, and not later than 10 days after identification of the SAE. The nature, severity, timing and relationship of the AE to circumcision or study medications is specified by the medical officer. A summary of how the severity and relationship to study participation was determined is provided by the PI, and clarifications are made by phone with the medical officer as needed.

.

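### Table 3 and the general severity rule disagree on bed rest, and Table 3 grades re-operation inconsistently, so like events may be reported differently and some may miss expedited SAE notice

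*Protocol*

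**What the plan says.** The protocol grades adverse events in two places.

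Section 7.4.2 (Severity of AEs) gives a general rule:
- mild: "transient and not affecting activity";
- moderate: "requiring modification of activity or additional medical /minor surgical/intervention";
- severe: among other outcomes, "incapacitating symptoms which require bed rest, hospitalization, significant medical/surgical interventions".

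Table 3 (Study Definition of Adverse Events) gives a grade and a code for each event type. In the first month after surgery, "Symptoms of pain requiring bed rest for less than half the day" is mild (BPA1). Bed rest for more than half a day is moderate (BPA2), and only excruciating pain with total bed rest is severe. For insufficient skin removed, "Prepuce still partially covers the glans and re-operation is required to correct" is moderate, both in the first month (BIS2) and later (CIS2), and the severe row is marked as not applicable.

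Reporting then follows the grade. Section 7.4.2 states: "All severe occurrences are considered serious adverse events (SAEs) for reporting purposes". Section 7.5.3 (Reporting of AEs) states: "All deaths and SAEs are notified to the Ugandan and U.S. PIs within 48 hours"; written notice to the IRBs follows within 10 days. Section 7.4.4 adds a catch-all, but only for serious events that Table 3 does not define. No section says whether the general rule or Table 3 prevails.

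**The concern.** A medical officer who applies the general rule and one who applies Table 3 can grade the same event differently. Two men with the same consequence, a re-operation, can also receive different grades within Table 3 itself. Because SAE status is attached to the severe grade, such a difference decides whether the PIs and IRBs hear of the event on the expedited route. Severity also enters the tabulations sent to the DSMB (section 7.5.4), the comparison with the 0.5% limit (sections 8.1.1 and 8.1.2), and the reported moderate and severe rates of 3.2% in HIV-positive men and 3.6% in HIV-negative men (section 10.7.3).

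The matter is still live. Enrolment has closed, but section 6.1b offers further surgery to uncircumcised men, and HIV-positive men now have weekly wound visits. The list of new AE codes concedes that the definitions could be improved for monitoring surgery in controls, yet leaves them unchanged.

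**Working it through.** The check is mainly textual, because the plan gives no figure for this point.

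**Step 1. Bed rest**

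| Code | Table 3 criterion | Table 3 grade | General rule in 7.4.2 |
| --- | --- | --- | --- |
| BPA1 | bed rest, under half a day | mild | not mild, since activity is affected; severe only if incapacitating |
| BPA2 | bed rest, over half a day | moderate | severe if incapacitating; otherwise can be moderate |
| (no code) | total bed rest | severe | severe |

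BPA1 contradicts the definition of mild outright. BPA2 conflicts with the severe definition whenever pain that keeps a man in bed for most of the day counts as incapacitating, and the protocol does not say when it does.

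**Step 2. Re-operation**

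| Code | Event type | Trigger | Grade |
| --- | --- | --- | --- |
| BIS2, CIS2 | insufficient skin removed | prepuce still partly covers the glans and re-operation is needed | moderate, no severe grade |
| BDW3, CDW3 | delayed wound healing | re-operation alone | severe |
| CAP3 | appearance, one month or later | re-operation alone | severe |

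This conflict lies inside Table 3 and does not depend on how significant surgery is understood in 7.4.2.

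**Step 3. Reporting chain.** Severe leads to SAE, which leads to 48-hour notice and then to the IRB report. An event coded BPA2, BIS2 or CIS2 does not enter this chain through its grade. The catch-all in 7.4.4 does not reach it either, because Table 3 defines it. The remaining route is the list of outcome criteria in 7.4.2: life-threatening, hospitalization, disability, and intervention to prevent permanent impairment. The text presents these as explaining why severe events count as SAEs, and does not say whether they apply to an event that Table 3 grades lower.

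**Step 4. Which counts move.** Let M be the number of moderate events and S the number of severe events. The monitored figure is M + S. Regrading one BPA2, BIS2 or CIS2 event to severe gives (M − 1) + (S + 1) = M + S, so the pooled count does not change; only the SAE count and the split by severity do. Regrading one BPA1 event to moderate gives (M + 1) + S, so the pooled count rises by one.

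**Step 5. What one event can do.** For the first 100 surgeries, Table 4 gives exact one-sided p-values against 0.5% of 0.0898 for 2 events and 0.0141 for 3. These reproduce:
- P(X = 0) = 0.995^100 = 0.6058
- P(X = 1) = 100 × 0.005 × 0.995^99 = 0.3044
- P(X = 2) = 4,950 × 0.005² × 0.995^98 = 0.0757
- P(X ≥ 2) = 1 − 0.6058 − 0.3044 = 0.0898
- P(X ≥ 3) = 0.0898 − 0.0757 = 0.0141

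Near such a limit, a single BPA1 event could therefore change the reading. That look has passed, and the later rates of 3.2% and 3.6% are well above 0.5%, so the present relevance is to the reported rates. The number of circumcised HIV-positive men is not given. Assuming 500 (section 8.4 expects 500 HIV-positive men per arm), 3.2% is 16 men, and each further man adds 1/500 = 0.2 percentage points. With 400 it would be 1/400 = 0.25 points. The gap between the two reported rates is 0.4 points, or 2 men in 500. How many BPA1 events there were is not stated.

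**The case against.** The strongest reply is that the general rule is qualified. Severe needs symptoms that are incapacitating or interventions that are significant, and moderate expressly allows minor surgery and changed activity. This stands, and it rules out several readings that a reader might infer.

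- **That Table 3 grades events below severe although they plainly meet the severe definition.** No listed row must meet it. BPA1 fails the mild definition, but that does not make it severe, and BPA2 can be defended as moderate.
- **That every code involving further surgery is misgraded.** "swelling requiring surgical exploration but no evidence of active bleeding" (BSH2) and additional surgery for a bruise or abrasion (ADP2, BDP2) can be read as minor surgery. ADP2 is also an intra-operative code, so it is not a return to theatre. Some severe comparators, such as first-month appearance (BAP3) or dehiscence (BWD3), require more than re-operation. The clean contrast is BIS2 and CIS2 against BDW3, CDW3 and CAP3.
- **That these events escape SAE reporting altogether.** The protocol says that all severe events are SAEs, not that only severe events are. The outcome criteria in 7.4.2 may catch some of them, and all AEs reach the DSMB in aggregate under 7.5.4.
- **That the moderate/severe rate is understated across the board.** Step 4 shows that only BPA1 could move it.

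It can also be said that section 7.4.1 points to Table 3 for the definitions and 7.4.4 says officers are trained to classify events, so the specific table presumably governs. That is plausible but nowhere stated, and it would not resolve the conflict inside Table 3.

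**Conclusion.** The contradiction is in the text. It concerns four codes: BPA1 against the definition of mild, BPA2 against the severe definition where the pain is incapacitating, and BIS2 and CIS2 against other re-operation rows of the same table. The consequence is that like events may be reported differently and some may miss the 48-hour notice; the documents do not show that any did.

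For BPA2, BIS2 and CIS2 the effect is confined to the SAE count and the tabulation by severity. BPA1 alone could raise the pooled moderate/severe rate, by about 0.2 to 0.25 percentage points per man if 500 to 400 HIV-positive men were circumcised, and only for men with no other moderate or severe event. The total effect cannot be computed without a BPA1 count. This should be corrected while surgery continues, but it does not by itself overturn the reported safety rates.

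**What to change.** - Reconcile section 7.4.2, section 7.4.4 and Table 3 on bed rest and on re-operation, and state which text prevails when they differ. The grades themselves are for the sponsor to decide.
- State that the SAE outcome criteria already listed in 7.4.2 apply whatever the Table 3 code, so that the 48-hour and 10-day reports depend on them and not on the grade alone.
- Re-tabulate BPA1, BPA2, BIS2 and CIS2 for the DSMB both ways, as coded and under the general rule, for HIV-positive and HIV-negative men separately.
- In the same edit, align the IRBs named for SAE notice in 7.5.3 (Johns Hopkins, Columbia and the Uganda Virus Research Institute) with the continuing-review bodies in section 10.2 (SEC and WIRB); WIRB is not on the SAE list.

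The cost is a text and table edit, refresher instruction for the medical officers, and one re-tabulation of existing codes. There may be a few more expedited reports and a slightly higher moderate/severe rate.
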